**Fig. 1 Fig1:**
[figure not shown]
An outline of the procedures

**Table 4 Tab4:**
[figure not shown]
Schedule of enrolment, interventions, and assessments

*Abbreviations*: *SCORAD* Scoring Atopic Dermatitis, *CDLQI* Children’s Dermatology Quality Life Index, *NCT* number cancellation test, *AEs* adverse events

#### Sample size {14}

The sample size was calculated based on the primary outcomes, which were the change in the SCORAD score from baseline to the end of week 8. In our pilot trial [17], with 20 patients in the Longmu Tang group and 20 patients in the control group, the mean (± standard deviation) reductions in the SCORAD score after 8-week treatment were 20.76 ± 8.05 and 6.35 ± 8.69 in the Longmu Tang and control groups, respectively. In a previous study [22], the mean reduction in the SCORAD score in the Longmu Tang group was 15, with 31 patients in the Longmu Tang group and 31 patients in the control group. In another previous study [23], the mean reduction in the SCORAD score in the Longmu Tang group was 12.86, with 62 patients in the Longmu Tang group and 60 patients in the control group. Considering the three trials and number of patients in each of the three trials, we estimated the mean (± standard deviation) reduction in the SCORAD score after 8-week treatment in the experimental and control groups to be 15 ± 8.69 and 6.35 ± 8.69, respectively. Assuming an alpha risk of 5% and beta risk of 10% using the GPOWER software (version 3.1.9.7), a sample size of 46 (23 participants in each group) was calculated. Considering a 20% loss to follow-up, this trial will require 60 participants (30 participants in each group).

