### Outcomes {12}

#### Primary outcome

The primary outcome of the trial is the efficacy of the Longmu Tang granule in improving the clinical symptoms of patients with AD after 8 weeks of treatment. The main evaluation of the primary outcome will be the change in the SCORAD score [18] from baseline to the end of the 8-week treatment. SCORAD was proposed by the European Task Force on AD. SCORAD includes the area (A) and severity (B) of skin lesions and the subjective symptoms of pruritus and their effects on sleep (C). The *SCORAD* system is internationally recognised as the gold standard for AD scoring. The SCORAD score ranges from 0 (best) to 103 (worst), with a minimal clinically important difference (MCID) of 8.7 [19]. Higher scores indicate more severe symptoms. The SCORAD scores of the participants before and after treatment will be statistically analysed.

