#### Recruitment {15}

Sixty participants will be recruited from March 2021 to March 2022 at Xiyuan Hospital of China Academy of Chinese Medical Sciences via Internet advertisements (using WeChat) and posters in the hospital areas (e.g. the outpatient hall). Dermatologists will also ask the patients if they would like to participate in this trial during the treatment process of AD. A dermatologist will be responsible for screening potential participants and assessing whether they meet the eligibility criteria. A research assistant will provide the participant and their guardian with an informed consent form and explain it in detail. The informed consent form will cover the purpose, procedure, potential benefits, and risks of the trial. The research assistant will perform a baseline assessment of all participants (− 1 to 0 weeks) before randomisation. The following demographic and clinical characteristics of the participants at baseline will be recorded in the CRF: age, sex, race, birthplace, the body mass index (kg/m^2^), current address, history of allergic diseases, family history, severity of AD assessed by the SCORAD index (mild [0–24 score], moderate [25–50 score], severe [51–103 score]), quality of life assessed by the CDLQI, cognitive ability assessed by the NCT, and safety evaluation assessed by laboratory indices (full blood count and urine, kidney, and liver function test results). An outline of the procedure is illustrated in Fig. 1.

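### Eligibility starts at SCORAD 0, so children who cannot improve, or cannot reach the 8.7-point MCID, may be enrolled, and the 90% power is unsupported for a 0–50 population

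*Protocol article*

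**What the plan says.** Four places in the protocol article bear on this.

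- **Inclusion criteria:** a SCORAD score from 0 to 50 is eligible. There is no lower limit above the bottom of the scale.
- **Primary outcome:** the endpoint is "the change in the SCORAD score [18] from baseline to the end of the 8-week treatment". The same paragraph states: "The SCORAD score ranges from 0 (best) to 103 (worst), with a minimal clinically important difference (MCID) of 8.7".
- **Sample size {14}:** the pilot reductions were "20.76 ± 8.05 and 6.35 ± 8.69 in the Longmu Tang and control groups, respectively", with 20 patients per arm. Two further studies reported mean reductions of 15 and 12.86 in the Longmu Tang group. The plan then sets the mean "reduction in the SCORAD score after 8-week treatment in the experimental and control groups to be 15" and 6.35 points respectively, each with SD 8.69. With alpha 5% and beta 10%, this gives 46 participants, raised to 60 for 20% loss. No entry SCORAD is given for any of the three source studies.
- **Recruitment {15}:** severity at baseline is classed as "mild [0–24 score], moderate [25–50 score], severe [51–103 score".

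**The concern.** The endpoint is an absolute fall on a scale that stops at 0, so no child can fall by more than the entry score. An entry score of 0 leaves no room to improve, and an entry score below 8.7 leaves too little room to reach the MCID. Such children are eligible, and the sample size section does not mention the floor.

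Low entry scores are not far-fetched. The trial is aimed at mild-to-moderate disease, and children already under treatment for AD are invited. The washout for antihistamines, topical corticosteroids and calcineurin inhibitors is one week. The diagnostic criteria set no minimum severity score.

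The power is at stake. Each child at or near the floor can show little or no treatment benefit, and this pulls the difference between arms below the planned 8.65 points. With about 24 evaluable children per arm there is little slack: at SD 8.69, power is 0.88 for a difference of 8, 0.78 for 7 and 0.65 for 6.

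**Working it through.** **Inputs from the protocol.** Mean falls 15 and 6.35, so the difference is 15 − 6.35 = 8.65; SD 8.69 in each arm; two-sided alpha 0.05; 23 evaluable per arm; 30 randomised per arm; 20% loss, leaving 30 × 0.8 = 24; scale floor 0; MCID 8.7; eligible range 0–50.

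**Step 1: the protocol's own figure.** The two-sample t-test has noncentrality (difference/SD) × √(n/2) on 2n − 2 degrees of freedom. At n = 23 this is (8.65/8.69) × √11.5 = 0.995 × 3.391 = 3.38, which gives power 0.910. At n = 22 power is 0.897, so 23 per arm (46 in total) is the correct answer. Inflation gives 46/0.8 = 57.5, so 60 is adequate. Power on the protocol's inputs is 0.92 at 24 per arm and 0.97 at 30.

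**Step 2: who cannot respond.** The documents give no distribution of entry scores. If scores were spread evenly over 0–50 (assumption), 8.7/50 = 17.4% of children could not reach the MCID and 15/50 = 30% could not fall by 15.

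**Step 3: effect on power.** Assumption: each child's fall is drawn from the planned Normal(15, 8.69) or Normal(6.35, 8.69) and cannot exceed that child's entry score. The mean difference and pooled SD of the capped falls were simulated and put into the formula of Step 1. Normal entry scores are kept within 0–50.

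| Assumed entry scores | Difference | SD | Power, 23 per arm | Power, 24 per arm |
|---|---|---|---|---|
| No cap (as planned) | 8.65 | 8.69 | 0.91 | 0.92 |
| Uniform 25–50 | 8.6 | 8.6 | 0.91 | 0.92 |
| Normal(30, 10) | 8.0 | 8.3 | 0.89 | 0.91 |
| Normal(25, 10) | 7.4 | 8.0 | 0.87 | 0.88 |
| Uniform 0–50 | 6.7 | 8.05 | 0.79 | 0.81 |
| Uniform 0–24 | 4.7 | 6.7 | 0.65 | 0.67 |
| Uniform 8.7–50 | 7.7 | 8.1 | 0.88 | 0.90 |
| Uniform 15–50 | 8.2 | 8.3 | 0.91 | 0.92 |

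For the uniform 0–50 row, the noncentrality is (6.71/8.05) × 3.391 = 2.83, which gives 0.79.

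**Step 4: is it mild disease or very low scores?** The Normal(25, 10) and uniform 0–50 rows both have half of the children below 25, yet power is 0.87 in one and 0.79 in the other. They differ in the share below 8.7: about 5% against 17.4%. In the uniform 15–50 row about 29% of children are mild and power is still 0.91. The loss therefore follows the very low scores.

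**Step 5: a different response model.** Suppose instead that falls are proportional to the entry score, and that the planned 15 and 6.35 apply at a mean entry score of 30 or 37.5 (again assumptions). Power at 24 per arm is then about 0.52 to 0.65 for uniform 0–50 and 0.91 to 0.98 for uniform 25–50. The capped model is thus not the most pessimistic choice for a population with many low scores.

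**The case against.** A reader might go further and conclude that the trial does not have its stated 90% power, or that it keeps that power only if hardly any mild child is enrolled. The documents support neither reading.

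- The 46 follows correctly from its inputs. Any loss depends on an entry-score distribution that the protocol does not report, and some plausible distributions leave power at about 0.90. This stands.
- Mild disease as such does little harm, as Step 4 shows. This stands.
- The planned 15 is an arm mean with SD 8.69, so about half of treated children are expected to fall by less. A child who cannot fall by 15 does not break an assumption; power rests on the difference between arms. This stands.
- The source studies used the same floored scale. If they enrolled a similar mix, the floor is already in their means, and capping again counts it twice. This may be so, but the protocol gives no entry scores by which to tell. The pilot's mean fall of 20.76 shows only that its Longmu Tang arm started at 20.76 or more on average, which still lies within the mild band. Weighting the three studies by Longmu Tang patients gives (20 × 20.76 + 31 × 15 + 62 × 12.86)/113 = 14.8, so 15 is a fair summary of them.
- A child must also meet at least three major and three minor diagnostic criteria and have the TCM syndrome, so scores near 0 should be uncommon. They are nevertheless not excluded.
- If no child were lost, 30 per arm would give 0.89 even for uniform 0–50. True, but that spends the whole allowance for loss to follow-up.

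These points limit how large the loss can be said to be. None of them removes the mismatch between the eligible range and the endpoint.

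**Conclusion.** The point holds in this form: the entry rule admits children who cannot improve on the primary endpoint, or cannot reach the MCID, and the sample size section neither addresses the floor nor gives entry scores that would show its effect estimate fits a 0–50 population. The 90% power is therefore unsupported for that population, not shown to be missed.

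Under the capped model at 23 per arm, power runs from 0.91 when entry scores are moderate (25–50) to 0.79 when they are even over 0–50, and to 0.65 in the extreme case of all scores even over 0–24. The absence of a lower limit is certain from the text. The size of the loss is not, because it rests on assumed entry-score distributions and an assumed response model.

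**What to change.** **Preferred.** In the inclusion criteria, replace the lower SCORAD limit of 0 with a justified limit above the 8.7-point MCID. Under the capped model with scores even over 8.7–50, power is about 0.88 at 23 per arm and 0.90 at the 24 left after 20% loss. The cost is one amended line, a few very mild children not enrolled and slightly slower recruitment. Recruitment opened in March 2021, so an amendment would affect only children not yet enrolled.

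**If 0 is kept.** In Sample size {14}, give the entry SCORAD of the three source studies where available. Re-derive the difference, SD and power for the expected mix of entry scores, and show the range with its assumptions. The 0.79 should not be written in as a fact, since it belongs to one assumed distribution. This costs only the rewriting.

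The severity bands in Recruitment {15} need no change. They include a severe band that is not eligible, so they describe severity and do not set entry.

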#### Recruitment {15}

Sixty participants will be recruited from March 2021 to March 2022 at Xiyuan Hospital of China Academy of Chinese Medical Sciences via Internet advertisements (using WeChat) and posters in the hospital areas (e.g. the outpatient hall). Dermatologists will also ask the patients if they would like to participate in this trial during the treatment process of AD. A dermatologist will be responsible for screening potential participants and assessing whether they meet the eligibility criteria. A research assistant will provide the participant and their guardian with an informed consent form and explain it in detail. The informed consent form will cover the purpose, procedure, potential benefits, and risks of the trial. The research assistant will perform a baseline assessment of all participants (− 1 to 0 weeks) before randomisation. The following demographic and clinical characteristics of the participants at baseline will be recorded in the CRF: age, sex, race, birthplace, the body mass index (kg/m^2^), current address, history of allergic diseases, family history, severity of AD assessed by the SCORAD index (mild [0–24 score], moderate [25–50 score], severe [51–103 score]), quality of life assessed by the CDLQI, cognitive ability assessed by the NCT, and safety evaluation assessed by laboratory indices (full blood count and urine, kidney, and liver function test results). An outline of the procedure is illustrated in Fig. 1.

### Assignment of interventions: allocation

#### Sequence generation {16a}

The random code will be generated by an independent statistician from the Good Clinical Practice (GCP) Centre of Xiyuan Hospital of China Academy of Chinese Medical Sciences. Participants will be randomly assigned to either the treatment or placebo group, at a ratio of 1:1 and a fixed block of 4.

#### Concealment mechanism {16b}

The number of randomisation sequences and information regarding group allocation will be placed in ordered envelopes and subsequently sealed to ensure randomisation concealment. The medicines will be labelled with random codes on the small and large packages by GCP specialists of the Xiyuan Hospital of China Academy of Chinese Medical Sciences.

#### Implementation {16c}

All participants and researchers will be blinded to the group assignment until trial completion. The same blinding code generated by the statisticians will be provided to the research institution and will not be broken during the trial period, except in the case of a serious adverse event that requires urgent breaking of the blinding code.

### Assignment of interventions: blinding

#### Who will be blinded {17a}

All participants and researchers will be blinded until the trial is completed.

#### Procedure for unblinding if needed {17b}

An emergency envelope contains randomised codes and group information corresponding to each patient. Once a serious event occurs and patients need to be treated, the project leader will decide to initiate unblinding and open the corresponding emergency envelope. Then the case will be treated as a shredded case.

### Data collection and management

#### Plans for assessment and collection of outcomes {18a}

The assessment and collection of outcomes are described in the outcomes section {12}, and at each visit, data will be recorded in the CRF, which can be provided by the corresponding author.

#### Plans to promote participant retention and complete follow-up {18b}

To maximise compliance and retention throughout the study, researchers will ensure that the study schedule and participation requirements are fully explained before consent is obtained and that participants are aware of the potential risks and benefits of the treatment. Each participant will be provided with a copy of the signed informed consent form, containing the contact information of the investigators, so that they can contact the primary investigators if required. Moreover, all participants will receive phone calls before each visit to remind them of their time. The participants will undergo free examinations and study medicine.

#### Data management {19}

Data will be imported into Epidata software (Doctors Without Borders) by two independent researchers. All researchers will receive professional training about correct assessments, procedures regarding the use of the study medicine, CRF completion, and use of the Epidata before and during this trial. Auditors from the Capital’s Funds for Health Improvement and Research will supervise all trial-related procedures and data management.

#### Confidentiality {27}

All participants’ data will be collected in a specific reception room instead of in public areas to avoid revealing their personal information to others. Initials of patient names will be used on the CRF, and all documents will be stored confidentially and accessible only to members of this study. Personal information about the potential and enrolled participants will only be consulted by the researchers of this study and will not be shared.

#### Plans for collection, laboratory evaluation, and storage of biological specimens for genetic or molecular analysis in this trial/future use {33}

Not applicable. This trial will not involve biological specimen collection for genetic or molecular analysis.

### Statistical methods

#### Statistical methods for primary and secondary outcomes {20a}

Data analysis will be completed using the Statistical Package of Social Sciences software (version 22.0; IBM Corp.), according to the per-protocol and intention-to-treat principles. Normally distributed continuous variables will be reported as mean ± standard deviation, and non-normally distributed continuous variables will be reported as median (interquartile range). The two-independent sample *t*-test, Wilcoxon test, or paired *t*-test will be used to analyse continuous variables, and the chi-square test and Fisher exact probability test will be used to analyse categorical variables. The two-sided test will be used uniformly in the hypothesis testing. A *P-*value < 0.05 will indicate that the difference is statistically significant, and a *P*-value < 0.01 will indicate that the difference is highly statistically significant.

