#### Secondary outcomes

The change in the Children's Dermatology Life Quality Index (CDLQI) score [20] (from baseline to week 8): the CDLQI is the most commonly used life index score of dermatological quality. This study will recruit children aged 6–12 years, so the CDLQI score will be used. The total CDLQI score ranges from 0 (best) to 30 (worst), with 6 as the MCID [21].The change in the number cancellation test (NCT) score (from baseline to week 8): the NCT is a traditional method used to evaluate attention function; the NCT score will be measured before and after the treatment, respectively, for 3 minutes each time, including the NCT net score and cancellation error rate, number of times of correct cancellation (the greater the better), number of times of incorrect cancellation, and number of times of omitted cancellation (the less the better), which will be compared before and after treatment. Raw score = the number of times of correct cancellation; net score = raw score – (the number of times of incorrect cancellation + 1/2 of the number of times of omitted cancellation); error rate = (the number of times of incorrect cancellation + 1/2 of the number of times of omitted cancellation) / raw score × 100%.Participants’ expectations of the Longmu Tang granule will be assessed at baseline using the following two questions: “Do you think the Longmu Tang granule will be effective for treating the illness?” and “Do you think the Longmu Tang granule will be effective for relieving the related symptoms of AD?” The response options will be ‘yes’, ‘no’, or ‘unclear’.Integral TCM syndrome score (from baseline to week 8 and 12; the scores and details are presented in Tables 2 and 3). A scale of 0–6 points is used to score patients with AD according to the severity of clinical symptoms.Significantly effective: inhibition or complete suppression of primary and secondary clinical symptoms and reduction of the syndrome score by ≥ 95%Effective: significant improvement in clinical symptoms and reduction in the syndrome score by 70–95%Ineffective: improvement in clinical symptoms and reduction in the syndrome score by 50–70%Invalid: reduction of treatment syndrome score by < 50%Long-term control: the evaluation of long-term control will be based on the change in the SCORAD score and change in the CDLQI score from baseline to the end of the 8-week follow-up after treatment.

**Table 2 Tab2:** Traditional Chinese medicine syndrome score

	None	Mild		Moderate		Severe	

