#### Participant timeline {13}

The visit schedule for all assessments (baseline, primary outcome, secondary outcomes, exploration outcomes, and security indicators) is shown in Fig. 1. At each assessment timepoint, the same investigator will evaluate the participants. During the treatment period (i.e. from baseline to week 8), all combined therapeutic medicines will be recorded, including their name, dose, and course. Participants’ expectations of the Longmu Tang granule will be assessed at baseline. The primary outcome and CDLQI score will be evaluated at baseline and at the first, second, fourth, sixth, and last visits. Exploratory outcomes, NCT scores, and safety indicators will only be evaluated at baseline and at the last visit. Table 4 summarises the schedule of screening, enrolment, intervention, assessments, and data collection.

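### The plan lists three unadjusted tests for continuous outcomes without naming the primary one; baseline-adjusted ANCOVA would be more precise, and the paired t-test should be labelled descriptive

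*Protocol article*

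**What the plan says.** Under Primary outcome, the article defines the endpoint as a change score: "The main evaluation of the primary outcome will be the change in the SCORAD score", taken from baseline to the end of the 8-week treatment. The same paragraph ends: "The SCORAD scores of the participants before and after treatment will be statistically analysed". For the number cancellation test (NCT), Secondary outcomes says of the measures: "which will be compared before and after treatment".

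The section headed Statistical methods for primary and secondary outcomes {20a} gives the tests: "The two-independent sample *t*-test, Wilcoxon test, or paired *t*-test will be used to analyse continuous variables". It adds "The two-sided test will be used uniformly in the hypothesis testing". It does not assign any of the three tests to the primary endpoint and names no covariate.

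Baseline SCORAD is available. Participant timeline {13} says "The primary outcome and CDLQI score will be evaluated at baseline and at the first, second, fourth, sixth, and last visits", and Recruitment {15} places the baseline assessment before randomisation. Inclusion criteria admit SCORAD from 0 to 50. Sequence generation {16a} gives a fixed block of 4 and mentions no stratification by severity.

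The hypothesis is framed against placebo, and Sample size {14} sets the mean reductions "in the experimental and control groups to be 15 ± 8.69 and 6.35 ± 8.69, respectively".

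**The concern.** Two separate matters meet in one sentence of {20a}.

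The first is precision. Of the three tests, only the two-sample t-test and the Wilcoxon test (in its two-sample form) compare the randomised arms, and neither adjusts for baseline. Baseline SCORAD may vary widely within the eligibility range. A child who enters below 15 cannot show the 15-point fall assumed for the active arm, so some association between baseline and change is plausible. In a trial of 60 children, a covariate measured before randomisation is a cheap source of precision and also corrects for chance imbalance more fully than subtracting baseline does.

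The second is the meaning of a listed test. A paired t-test asks whether one arm changed over time. It absorbs regression to the mean, natural course and, for the NCT, any practice effect. Listed without qualification for primary and secondary outcomes, and next to outcome text about scores before and after treatment, it leaves room for within-arm P values to be offered as evidence of efficacy.

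**Working it through.** **Inputs.** From Sample size {14}: mean reductions 15 and 6.35, SD 8.69 in each arm, alpha 5%, beta 10%, 23 per arm evaluable, 20% loss, 60 in total. From {20a}: two-sided testing. The pilot control arm (n = 20) also showed 6.35 ± 8.69. The article gives no correlation between baseline and change, so r below is an assumption, shown over a range.

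**1. The plan's own figure.** Difference = 15 − 6.35 = 8.65; standardised, 8.65/8.69 = 0.995. For a two-sided two-sample t-test at 0.05, the noncentral t gives power 0.897 with 22 per arm and 0.910 with 23. The stated 23 per arm (46) is reproduced. Loss: 46/0.8 = 57.5, so 58; the planned 60 covers it. The sample size therefore rests on an unadjusted between-arm comparison of change, and that comparison meets its target.

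**2. Adjusting for baseline.** In ANCOVA the residual SD is 8.69 × √(1 − r²), where r is the within-arm correlation of baseline with change, and one degree of freedom is lost. Power uses the noncentral t with noncentrality 8.65/(SD × √(2/n)); the half-width is that of the 95% CI at 23 per arm.

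| r (assumed) | Residual variance ratio | Residual SD | Power, 23 per arm | n per arm for 90% | CI half-width |
|---|---|---|---|---|---|
| unadjusted | 1.00 | 8.69 | 0.910 | 23 | 5.16 |
| 0.1 | 0.99 | 8.65 | 0.912 | 23 | 5.14 |
| 0.2 | 0.96 | 8.51 | 0.920 | 22 | 5.06 |
| 0.3 | 0.91 | 8.29 | 0.933 | 21 | 4.93 |
| 0.5 | 0.75 | 7.53 | 0.968 | 17 | 4.48 |
| 0.6 | 0.64 | 6.95 | 0.985 | 15 | 4.13 |

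The same gain can be written in terms of rho, the correlation between baseline and week-8 SCORAD. With equal variances at the two times, the variance ratio is (1 + rho)/2: 0.65, 0.75 and 0.85 for rho = 0.3, 0.5 and 0.7, with power 0.98, 0.97 and 0.95 at 23 per arm. The two forms agree; rho = 0.5 corresponds to r = 0.5.

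**3. The paired test on the planned placebo change.** t = 6.35/(8.69/√n).

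- n = 20 (the pilot control arm): t = 6.35/1.943 = 3.27, P = 0.004.
- n = 23: t = 6.35/1.812 = 3.50, P = 0.002; probability of P < 0.05 is 0.92.
- n = 30: t = 6.35/1.587 = 4.00, P = 0.0004; probability of P < 0.05 is 0.97.

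These P values are for a sample that shows exactly the assumed mean and SD. The probabilities allow for sampling variation when the assumption is true. All three P values fall below 0.01, the level to which {20a} attaches its stronger significance label.

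**The case against.** The strongest reply is that the two-sample t-test on change is valid under randomisation, matches the basis of the sample size and reaches 91% power at 23 per arm (97% if all 30 per arm are analysed). Lack of adjustment costs precision and causes no bias. The gain depends on an unknown correlation and is slight at the low end of the range. Covariates are often left to an analysis plan, which is not shown here. All of this stands, and it keeps the point to an improvement in method. What remains is that the article does fix a list of tests for the primary and secondary outcomes, all unadjusted, while a baseline covariate is already in hand.

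Four stronger readings are tempting, and the article does not support them:

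- **That the paired t-test is the planned test of the primary outcome.** No section assigns it. The hypothesis, the choice of comparator and the sample size are all between-arm, and the before-and-after phrases follow text that defines change endpoints. The test may be meant for within-arm description.
- **That the planned analysis ignores baseline.** A change score subtracts it; ANCOVA simply uses it more efficiently.
- **That change must correlate with baseline because the score stops at 0.** The floor makes this likely but does not prove it or give its size. No baseline distribution is shown, and if most children enter in the 25 to 50 band the floor would seldom matter.
- **That the intermediate SCORAD values go unused.** Nothing says so. The multiple imputation in {20c} could draw on them, and a single week-8 primary time point is legitimate.

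**Conclusion.** The concern holds in a limited form. Section {20a} leaves the primary test open among three and names no baseline adjustment. Its two-sample t-test is sound and supports the planned size, but ANCOVA on baseline SCORAD would be at least as good at almost no cost: power at 23 per arm moves from 0.91 to between 0.91 and 0.98 for r between 0.1 and 0.6. That range is an assumption; the article supplies no correlation.

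The paired t-test cannot answer the trial's question. The 92% to 97% chance of a significant placebo result follows from the article's own 6.35 ± 8.69, and it does harm only if within-arm P values are presented as efficacy evidence. The article does not say that they will be, and it does not rule it out.

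**What to change.** In {20a}, state that the primary analysis is a between-arm ANCOVA of week-8 SCORAD (or its change from baseline) on treatment arm and baseline SCORAD, reported as the adjusted mean difference with a 95% CI. Use the same model for CDLQI and NCT, each with its own baseline value. State that within-arm before-after tests are descriptive only and will not support a claim of efficacy, and align the closing sentence of Primary outcome and the NCT text with this. A mixed model over all visits, or age as a further covariate for the NCT, is optional.

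The covariates are already collected, the SPSS package named in {20a} can fit the model, and the sample size stays at 60. Because recruitment began in March 2021, the cost is a protocol wording change notified to the ethics committee and the funder under the amendment section {25}, ideally made before unblinding.
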